#### Intervention Structure and Delivery

The intervention consists of 4 modules. The first module utilizes a combination of lectures, PowerPoint presentations, and a question-and-answer session to provide a foundational understanding of childhood TB. The duration of this module is estimated to be 30 minutes. The second module concentrates on understanding the BCG vaccine and TB prevention practices. The delivery method is similar to that of the first module and takes approximately 30 minutes. The third module explores participants’ attitudes toward the BCG vaccine and TB prevention practices. Various strategies are used, including video presentations featuring traditional and religious leaders, interactive sessions, and brainstorming exercises. This module is estimated to take 1 hour to be completed. The fourth and final module aims to enhance participants’ self-efficacy regarding the BCG vaccine and TB prevention practices, as well as equip participants with useful skills to make informed decisions and overcome potential challenges. This module incorporates a diverse range of strategies, including role-play videos, interactive sessions, and brainstorming exercises. The duration of this module is estimated to last 1 hour and 30 minutes.

Participants in the intervention group were divided into 6 small groups for health education sessions. There were 6 intervention sessions, with 1 group per session; each session accommodated 30 participants, except for the first session, which had 35 participants. The language of delivery was Somali, and participants received US $2.00 for transportation. The delivery of the modules was closely monitored and supervised by the researchers, who provided necessary feedback to the facilitators to ensure strict adherence to the protocol without deviation. After the completion of the sessions, mothers participating in the intervention received a follow-up call 1 month later to reinforce the key points discussed and to highlight the importance of prioritizing the administration of the BCG vaccine for their newborns.

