### Sample Size

The 2-sample mean formula was used to determine the sample size for this study. This formula considers the mean and SD of TB preventive practices from a previous health education program conducted by John [19], where a SD of 4.40, an intervention group mean of 20.71, and a control group mean of 18.45 were used in the calculation. To ensure adequate statistical power, several adjustments were made for the estimated eligibility (90%) and attrition rate (30%), with a 95% significance level and 80% desired power. The anticipated high attrition rate is primarily due to the impact of the COVID-19 pandemic, which created significant barriers to participation in the study. Based on this formulation, the total sample size for this study was 370 participants, with an equal number of participants in both the intervention and control groups.

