### Randomization, Allocation Concealment, and Blinding

Randomization was performed at the individual level, with pregnant women as the sampling unit. Ensuring an equal allocation ratio (1:1), participants were randomly assigned into the intervention group, which received the IMB-based health education intervention, or the control group, which was placed on a waiting list. The randomization process was conducted using computer-generated random numbers using a web-based calculator (GraphPad; GraphPad Software) by hospital staff who were independent of all other research processes. The generated sequences were placed in sealed opaque envelopes. Subsequently, another hospital staff member, who was also independent of the research team, was responsible for opening the envelopes sequentially and assigning participants to either the intervention or control group.

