#### Control Group

The control group was assigned to a waiting list status throughout the intervention program. Participants received their usual care during their visits to the ANC clinic and had access to general health education content through television programming. The hospital does not provide personalized health education for antenatal mothers. To avoid potential contamination or cross-group influence, participants in both groups were given different follow-up dates. Additionally, participants were clearly instructed on the importance of not discussing the intervention sessions with others.

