### Data Analysis

Collected data were entered into SPSS software (version 27.0; IBM Corp) before proceeding with data cleaning procedures. Both statistical and graphical normality tests were applied to continuous variables, such as age, knowledge, attitude, and self-efficacy. At baseline, the comparison of variables between groups used appropriate statistical measures based on the distribution of data. For normally distributed data, results are reported as mean (SD), and comparisons were conducted using an independent *t* test. For non-normally distributed data, results were reported as median (IQR), and comparisons were conducted using the chi-square test and the Mann-Whitney *U* test.

To evaluate the main effect of the IMB-based intervention modules on the response variables over time, as well as the group-time interactions, repeated-measures ANOVA was used for normally distributed data. For non-normally distributed data, generalized linear mixed models were applied to account for individual-level variability among participants, or generalized estimating equations were used when focusing on overall population-level trends. Intention-to-treat analyses were conducted separately for the intervention and control groups, and missing data were addressed using multiple imputations. Results were reported as differences between groups with 95% CIs. Statistical significance in this study was set at α=.05.

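### The post-intervention analyses leave out the six teaching sessions in the intervention arm, so confidence intervals are too narrow if outcomes correlate within sessions

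*Protocol article*

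**What the plan says.** All references are to the Protocol article; no separate analysis plan is at hand.

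- **Unit of randomization** (Randomization, Allocation Concealment, and Blinding): "Randomization was performed at the individual level, with pregnant women as the sampling unit", in a 1:1 ratio.
- **Delivery** (Intervention Structure and Delivery): "There were 6 intervention sessions, with 1 group per session; each session accommodated 30 participants", apart from 35 in the first. The sizes add up to the whole arm: 35 + 5 × 30 = 185. Of the last module the article says: "This module incorporates a diverse range of strategies, including role-play videos, interactive sessions, and brainstorming exercises". Table 1 also lists discussion and brainstorming for module 3.
- **Controls** (Control Group): "The control group was assigned to a waiting list status throughout the intervention program". They had usual antenatal care and were not formed into groups.
- **Analysis** (Data Analysis): repeated-measures ANOVA for normally distributed outcomes. For the rest, "generalized linear mixed models were applied to account for individual-level variability among participants", or GEE when population-level trends are of interest.
- **Sample size** (Sample Size): "The 2-sample mean formula was used to determine the sample size for this study", with allowances for eligibility and attrition only.

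The article nowhere mentions a session effect, an ICC or a design effect.

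**The concern.** This is a partially nested design: independent women at randomization, clusters in one arm afterwards. Women in one session share peers, discussion, date and the delivery of that day. Modules 3 and 4, which rely on interaction, take 1 h + 1 h 30 min of the 3 h 30 min total. Some similarity of later outcomes within a session is therefore plausible. Individual randomization does not remove it, because it arises after allocation.

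The only dependence that the stated methods address is that between repeated measurements of the same woman. An ordinary repeated-measures ANOVA has no place for a random effect that exists in one arm only, and the variability described for the GLMM is the participant's. At stake are the coverage of the 95% CIs and the error rate of the tests for both primary outcomes and all three secondary scores at 2 and 4 months.

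**Working it through.** **Inputs.** From the article: 185 per arm; session sizes 35, 30, 30, 30, 30, 30; SD 4.40; difference 20.71 − 18.45 = 2.26; α = 0.05 (two-sided assumed); power 80%; eligibility 90%; attrition 30%. Assumed, because the article gives none: ICC of 0.01, 0.02 and 0.05 for the outcome as analysed. Equal outcome variance in the two arms is also assumed.

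**The plan's own figure.** n per arm = 2 × (1.96 + 0.84)² × 4.40² / 2.26² = 59.5, so 60. Inflated, 60 / 0.9 / 0.7 = 95.2 per arm, about 190 in total. The stated 370 is not reproduced; it is about twice that. This is a separate matter. It bears on the present point only because the surplus protects power.

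**Design effect, intervention arm only.** The effective session size is m = Σmᵢ² / Σmᵢ = (35² + 5 × 30²) / 185 = 5725 / 185 = 30.9. After 30% attrition it is 0.7 × 30.9 = 21.7, with about 130 women per arm.

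- DE = 1 + (m − 1) × ICC
- SE ratio (correct / unadjusted), equal arms = √[(DE + 1) / 2]
- True error of the unadjusted test = 2 × [1 − Φ(1.96 / SE ratio)]

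Example, ICC 0.05 with full follow-up: DE = 1 + 29.9 × 0.05 = 2.50; SE ratio = √(3.50 / 2) = 1.32; 1.96 / 1.32 = 1.48; error = 13.8%.

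| Follow-up | ICC | DE | SE ratio | Error, formula | Error, simulated |
|---|---|---|---|---|---|
| Full (185 per arm) | 0.01 | 1.30 | 1.07 | 6.8% | 6.5% |
| | 0.02 | 1.60 | 1.14 | 8.6% | 8.4% |
| | 0.05 | 2.50 | 1.32 | 13.8% | 13.7% |
| After 30% attrition | 0.01 | 1.21 | 1.05 | 6.2% | 6.5% |
| | 0.02 | 1.41 | 1.10 | 7.4% | 7.6% |
| | 0.05 | 2.03 | 1.23 | 11.1% | 10.9% |

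The simulation used 20,000 trials per row, with session effects that vary around an average of zero. Coverage of a nominal 95% CI is one minus the error: about 93% down to 86% with full follow-up.

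**Which percentage is which.** With full follow-up the correct SE is 7%, 14% and 32% larger than the unadjusted one. Put the other way, the unadjusted SE falls short by 1 − 1/ratio: 7%, 12% and 24%.

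**Power of a session-adjusted analysis** for 2.26 points at ICC 0.05 after attrition:

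- SE = 4.40 × √[(2.03 + 1) / 129.5] = 0.67, and 2.26 / 0.67 = 3.36.
- The normal approximation gives about 92%.
- With Satterthwaite degrees of freedom (5 for the session part, about 11 overall) it is about 86%.
- At ICC 0.01 and 0.02 it is about 96% and 94%. At 0.10, beyond the assumed range, it would be about 73%.

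**The case against.** **The ICC may be small.** A reader might infer that the SEs are certainly too small. The article does not support that, because it reports no ICC, and at zero there is no harm. Several features point to a low value. Each group met once, for about three and a half hours. Much of the content was lecture, slides and video. Delivery was supervised for adherence, and reinforcement was by telephone call. Outcomes were measured 2 and 4 months later. Two interns are described, and nothing says that facilitators differed between sessions. This stands, and the conclusion must be conditional. The interactive modules equally prevent assuming zero.

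**The error figures need a particular null.** A reader might infer that an ineffective programme would be declared effective 7% to 14% of the time. That does not follow. With individual randomization, if the education changes nobody's outcome, session membership changes nothing and an ordinary two-arm test keeps about 5%. The figures apply when sessions have real but differing effects that average zero. This stands too. Undercoverage of the CIs whenever effects vary by session is not touched by it.

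**Not every analysis is affected.** The baseline comparisons precede the sessions and are sound in this respect.

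**An unseen analysis plan may add the term.** The exact random-effects structure is often left to such a plan. But the article commits to repeated-measures ANOVA, which an analysis plan would have to replace rather than elaborate. For the GLMM it names the participant as the level of variability.

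**The adjustment is imprecise.** With six groups and a true ICC of 0.01 to 0.02, the estimated session variance is zero or negative in about 31% to 42% of trials with full follow-up. The adjusted model then often returns the unadjusted answer. This is a fair limit on the remedy, and a reason to report the uncertainty.

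**Conclusion.** The point holds conditionally. The partially nested structure and the missing session term are plain from the article; the harm depends on a positive within-session ICC, for which 0.01 to 0.05 is an assumption. Over that range the post-intervention SE should be 1.07 to 1.32 times the unadjusted one with full follow-up, or 1.05 to 1.23 times after the planned attrition, and the 95% CIs undercover accordingly. Tests of a zero average effect have a true error of about 7% to 14% (6% to 11% after attrition) if session effects vary.

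A reader might also infer that the trial is underpowered once sessions are modelled. For the practices score the article's figures do not support this, since power stays above 80% up to an ICC of about 0.05. The article gives no planning figures for BCG uptake, so its power cannot be judged in this way. The point is a should-fix.

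**What to change.** For the post-intervention comparisons of practices, BCG uptake, knowledge, attitude and self-efficacy:

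1. Replace the repeated-measures ANOVA with a linear mixed model, and extend the GLMM, so that each has participant effects plus a session random effect in the intervention arm only. Each control is her own cluster.
2. Use small-sample degrees of freedom (Satterthwaite or Kenward-Roger) where available.
3. Report the session ICC with its uncertainty.
4. Do not rely on ordinary sandwich standard errors from GEE, which are unreliable with six clusters.

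**Cost.** No new data should be needed, provided session membership was recorded for the six groups. The CIs widen and the session variance is estimated imprecisely. This is a change of model for the normally distributed outcomes, not just an added term. Data collection ended in June 2022, so the change should be dated and declared as made after that. Under Ethical Considerations the article undertakes to report changes in analysis methods to the registry and the university ethics committee.

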#### Control Group

The control group was assigned to a waiting list status throughout the intervention program. Participants received their usual care during their visits to the ANC clinic and had access to general health education content through television programming. The hospital does not provide personalized health education for antenatal mothers. To avoid potential contamination or cross-group influence, participants in both groups were given different follow-up dates. Additionally, participants were clearly instructed on the importance of not discussing the intervention sessions with others.

### Data Collection

Data were collected using paper questionnaires at 3 distinct time intervals: baseline, 2-months postintervention, and 4-months postintervention. Participants were asked to complete a consent form before participating and were informed that their information would remain confidential and used solely for research purposes. The recorded data were securely stored in protected files, and individual responses were not reported publicly; instead, findings were presented in aggregate form. The random assignment took place on the same day that participants were selected for the study, after the collection of baseline data. To facilitate the data collection process, each participant was given a study follow-up card and was requested to carry them during each follow-up visit to the hospital.

### Quality Control

Several steps were taken to ensure the validity and reliability of the questionnaire. First, content and face validity were evaluated to ensure that the wording, ordering, and language were appropriate and well understood. The analysis categorized items as good, average, or poor; language clarity was assessed as clear, average, or confusing; and the appropriateness of construct measurement was classified as good, average, or poor. Feedback from experts and participants led to important modifications, including rewording several items for clarity and removing 3 items deemed irrelevant to the study objectives.

Additionally, factor analysis was conducted using SPSS software (version 27.0; IBM Corp) on a separate sample set of 134 participants who were not part of the main study but were recruited from the same hospital to assess sampling adequacy. Cohen’s κ and intraclass correlation coefficient values were also utilized to evaluate the reliability of the questionnaire. All values exceeded 0.60, which is considered acceptable [25].

### Outcome Assessment

Table 2 presents the primary and secondary outcome assessments, including the timing of each measurement.

**Table 2. T2:** Outcome measurements.

Outcome measure	Definition	Time of measurement		
		T0 (baseline)	T1 (2-month follow-up)	T2 (4-month follow-up)
Primary outcomes				
BCG^a^ uptake	Refers to receiving 1 dose of the BCG vaccine at birth. Infants who receive the vaccine after 6 weeks will be considered delayed.	No	Yes	Yes
TB^b^ preventive practices	Refers to the change in total practice scores of actions taken by participants to reduce the risk of TB infection and transmission, including respiratory hygiene (cough etiquette) and environmental control, between baseline, 2-month follow-up, and 4-month follow-up.	Yes	Yes	Yes
Secondary outcomes				
Knowledge	Refers to the total score change of participants’ knowledge regarding BCG vaccine benefit, schedule, and side effect, as well as knowledge of preventive practices (respiratory hygiene/cough etiquette and environmental control) between baseline, 2-month follow-up, and 4-month follow-up.	Yes	Yes	Yes
Attitude	Refers to the change in total attitude scores toward the BCG vaccine and preventive practices between baseline, 2-month follow-up, and 4-month follow-up.	Yes	Yes	Yes
Self-efficacy	Refers to the change in total scores reflecting participants’ confidence in their ability to obtain and receive the BCG vaccine, as well as their confidence in engaging in TB prevention practices between baseline, 2-month follow-up, and 4-month follow-up.	Yes	Yes	Yes

a BCG: Bacillus Calmette–Guérin.

b TB: tuberculosis.

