**Results:**

A total of 370 pregnant women were recruited at baseline in November 2021, with 185 assigned to the intervention group and 185 assigned to the control group. In January 2022, the 185 pregnant women enrolled in the intervention program and completed the sessions by February 2022. Data collection for the 2-month and 4-month postintervention assessments was completed in June 2022. The findings of this study will be reported by the beginning of 2026.

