### Study Population and Study Setting

The study population consists of pregnant women attending the Banadir Maternal and Child Hospital, Mogadishu, for ANC visits. The inclusion criteria include mothers with a gestational age range of 25 to 33 weeks, plans for postnatal follow-up at the hospital, and residence in Mogadishu, including internally displaced persons. The exclusion criteria include mothers who visited the hospital for other health conditions, those of non-Somali nationality, and those who had previous health education training related to immunization and TB prevention practices.

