## Results

Recruitment began on November 25, 2021, and by December 21, 2021, a total of 370 participants had been enrolled in the trial. The intervention sessions were completed on February 4, 2022. Follow-up data collection was completed on June 14, 2022. Results are expected to be published by the end of 2025.

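### BCG uptake is defined by infant age but read at visits timed from the sessions, so the 2-month reading is not interpretable for a substantial share of infants; the 4-month reading can carry the endpoint

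*Protocol article*

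**What the plan says.** In the protocol article, Table 2 (Outcome Assessment) lists BCG uptake first among the primary outcomes: "Refers to receiving 1 dose of the BCG vaccine at birth. Infants who receive the vaccine after 6 weeks will be considered delayed". The table marks it as not measured at T0 and as measured at both T1 and T2.

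The visits are timed from the intervention, under Data Collection: "Data were collected using paper questionnaires at 3 distinct time intervals: baseline, 2-months postintervention, and 4-months postintervention".

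The other dates needed are:
- Eligibility, under Study Population and Study Setting: "mothers with a gestational age range of 25 to 33 weeks".
- Enrolment, under Results: "Recruitment began on November 25, 2021, and by December 21, 2021, a total of 370 participants had been enrolled in the trial".
- Sessions, in the abstract's Results ("In January 2022, the 185 pregnant women enrolled in the intervention program and completed the sessions by February 2022") and in the main Results ("The intervention sessions were completed on February 4, 2022").
- End of follow-up, under Results: "Follow-up data collection was completed on June 14, 2022".
- Visit scheduling, under Control Group, as a guard against contamination: "participants in both groups were given different follow-up dates".

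Data Analysis describes modelling the response variables over time with a group-by-time interaction. It does not name BCG there, and it does not exclude it.

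**The concern.** The outcome runs on one clock, the infant's age, and the assessment runs on another, time since the sessions. Women differed by up to 8 weeks of gestation at entry, and entry itself was spread over nearly 4 weeks. A fixed visit therefore finds some infants well past the 6-week limit and others newborn or not yet delivered.

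A vaccinated infant can be scored at any visit. The difficulty lies with those recorded as unvaccinated at T1: not yet born, born but still within the 6 weeks, or missed. Only the last is the failure that the intervention is meant to prevent. If BCG is analysed at T1, or as a change from T1 to T2, much of what is measured is births and ageing. Infant age at the visit could also differ by arm if visit dates did.

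**Working it through.** **Inputs from the article.** Enrolment 25 November to 21 December 2021 (26 days); gestational age at entry 25 to 33 weeks; sessions from some day in January to 4 February 2022; follow-up ended 14 June 2022.

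**Assumptions, not in the article.** Enrolment dates and gestational ages uniform; delivery at mean 39.5 weeks, SD 1.5; T1 and T2 taken as 60 and 120 days after the session.

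**Formula.** Infant age at visit = visit date − [enrolment date + 7 × (weeks at delivery − weeks at enrolment)].

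**Extremes, with delivery at 40 weeks.**
- Earliest due date: 33 weeks on 25 November, plus 7 weeks = 13 January 2022.
- Latest due date: 25 weeks on 21 December, plus 15 weeks = 5 April 2022; this infant reaches 6 weeks on 17 May.
- Spread at any one visit date: 26 days + 8 × 7 days = 82 days = 11.7 weeks.

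Infant age on particular dates therefore runs:
- 1 March (two calendar months after a 1 January session): from 5.0 weeks before birth to 6.7 weeks.
- 4 April (two calendar months after 4 February): from about 0 to 11.6 weeks.
- 1 May (earliest T2): from 3.7 to 15.4 weeks.
- 14 June (end of follow-up): from 10.0 to 21.7 weeks.

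**Shares by simulation.** The article does not give the session calendar, so four possibilities are shown. The last takes T2 on the final day of follow-up and T1 60 days before it.

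| Calendar | T1 | Unborn at T1 | Unborn or under 6 weeks at T1 | Under 6 weeks at T2 |
|---|---|---|---|---|
| Sessions spread 1 Jan to 4 Feb | 2 Mar to 5 Apr | 12% | 73% | 2% |
| All sessions 1 Jan | 2 Mar | 32% | 94% | 9% |
| All counted from 4 Feb | 5 Apr | 1% | 46% | 0% |
| Counted back from 14 Jun | 15 Apr | 0.1% | 29% | 0% |

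**Sensitivity to delivery.** With mean 39 to 40 weeks and SD 1.7, the first row's T1 share is 67% to 77%, the second row's 90% to 95%, and the last row's 24% to 35%. The largest T2 share, with all sessions on 1 January and a mean of 40 weeks, is 13%. The highest unborn share at T1 is about 38% (40% if two calendar months are counted instead of 60 days).

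**T1 to T2.** In the spread calendar, 73% − 2% = 71% of infants pass the 6-week limit between the two visits. In the latest calendar it is 29%.

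**Sensitivity to visit date.** Moving T1 from 5 to 15 April lowers the share unborn or under 6 weeks from 46% to 29%: 17 points in 10 days, or about 1.7 points per day. At T2 the same 10-day shift, from 4 to 14 June, changes nothing, because the share is 0% on both dates.

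**Births before the session.** In the spread calendar about 8% of births precede the mother's session (0.4% if all sessions were on 1 January, 24% if all were on 4 February).

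**The case against.** Several points on the other side stand.

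- **Whether most infants are too young at T1.** A reader might infer that they are. That holds if sessions were spread through January, but the calendar is not documented. Counting T1 from the end of the sessions, or back from the end of follow-up, brings the share below half.
- **Whether the endpoint can be scored.** A reader might infer that it cannot. In fact a dose already given can be scored in any infant born, and at T2 nearly all infants are past 6 weeks. The fault lies in the T1 reading.
- **Doses between birth and 6 weeks.** Table 2 labels only later doses as delayed, so a dose within 6 weeks is naturally read as not delayed.
- **Bias between arms.** A reader might infer from the different follow-up dates that the comparison is biased. Women were individually randomised 1:1 from one population, so infant age is balanced in expectation. With comparable visit timing, ageing drives the time effect and creates no arm difference under the null. The article gives neither size nor direction for any gap in dates, which may mean only separate clinic days. The 1.7 points per day shows that T1 is sensitive to such a gap, not that a gap existed.
- **Condensed article.** Session dates and the scoring of undelivered women may be in the full protocol, and their absence here is no finding.

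The last point does not remove the concern. Table 2 itself sets an age-based definition beside visit-based readings at both T1 and T2.

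**Conclusion.** The concern holds for the T1 reading. A substantial share of infants are then unborn or under 6 weeks: about 73% with sessions spread over 1 January to 4 February, and roughly 29% to 94% across possible calendars. Unborn infants alone are a minority in every scenario. T1 uptake is a mixture, and its change to T2 largely reflects births and ageing. About 91% to 100% of infants are past 6 weeks at T2 under the main delivery assumption (87% in the most extreme case), so the primary outcome is recoverable there. Differential visit timing is a risk to the T1 contrast, not a demonstrated bias.

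The 12-week spread in infant age follows from the article's own dates. The percentages rest on the assumed delivery distribution, uniform entry and the unknown session calendar.

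**What to change.** Define the primary BCG endpoint once: BCG received by day 42 of life, yes or no. Day 42 is the plan's own 6-week limit. Score it for all randomised women from the vaccination date or age at vaccination obtained by T2, whatever the visit date. Then:
- Report later doses separately as delayed.
- Make T1 uptake descriptive, and state that BCG is not part of the group-by-time test.
- Treat infants who are under 6 weeks and unvaccinated at T2 as missing or censored, not as failures.
- Optionally, add a supportive analysis in both arms limited to women whose due date, from baseline gestational age, falls after 4 February 2022. Selecting on the baseline due date respects randomisation; selecting on actual delivery date would not.

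**Cost.** The T1 test is lost. Vaccination timing must have been recorded; the delayed category implies that it was, but the article does not say so. Data collection ended in June 2022, so a primary outcome is being specified afterwards. The change should be declared as such to the registry and the ethics committee before results are analysed or reported. Ethical Considerations already commits to notifying both of changes to outcomes or analysis methods.

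### BCG uptake is read at visits timed from the teaching session, not from birth, so many T1 negatives are premature; rest the primary comparison on T2 or one fixed infant age

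*Protocol article*

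**What the plan says.** The Abstract and Table 2 (Outcome Assessment) make BCG uptake one of two primary outcomes. Table 2 defines it as one dose at birth and adds: "Infants who receive the vaccine after 6 weeks will be considered delayed". The BCG row reads No at baseline and Yes at both T1 and T2.

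The visit clock is in Data Collection: "Data were collected using paper questionnaires at 3 distinct time intervals: baseline, 2-months postintervention, and 4-months postintervention". Women enter while pregnant; the criterion is "mothers with a gestational age range of 25 to 33 weeks" (Study Population and Study Setting). Data Collection also says: "The random assignment took place on the same day that participants were selected for the study, after the collection of baseline data". The enrolment date is therefore the baseline date.

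The dates are in the Results: "Recruitment began on November 25, 2021, and by December 21, 2021, a total of 370 participants had been enrolled in the trial" and "The intervention sessions were completed on February 4, 2022". Follow-up data collection closed on 14 June 2022. The Abstract places the start of the sessions: "In January 2022, the 185 pregnant women enrolled in the intervention program and completed the sessions by February 2022".

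For analysis, Data Analysis states one purpose for its longitudinal models: "To evaluate the main effect of the IMB-based intervention modules on the response variables over time, as well as the group-time interactions". It describes no separate analysis for BCG. The chi-square test appears only for baseline comparisons. No section names T1 or T2 as the decisive visit for BCG.

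**The concern.** The outcome runs on the infant's age and the visits run on the mother's session date. The two clocks are linked only through gestational age at entry, which spans eight weeks or more. At T1 a recorded no can mean three things: the baby is not born, the baby is born but not yet 6 weeks old, or the baby is past 6 weeks and was not vaccinated. Only the last is final under the Table 2 definition.

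The problem does not depend on the arms having different visit dates. It arises in both arms even with identical dates and one agreed reading of the definition.

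If BCG enters the longitudinal models as one of the response variables, a main effect over T1 and T2 includes a premature reading, and the time term partly measures babies being born and growing older. A real benefit could be understated. The article plans multiple imputation for missing data, but that cannot properly supply the status of an infant who does not yet exist.

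**Working it through.** **Step 1. Do the dates fit a session clock?** The last session was on 4 Feb 2022. Four months later is 4 June, 10 days before the stated close on 14 June. They fit.

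**Step 2. Infant age at T1, by hand.** Formula: infant age = gestational age at enrolment + weeks from enrolment to visit − gestational age at birth. Birth at 40 weeks is an assumption, and 1 January is taken as the earliest session day because the article gives only the month.

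| Woman | Enrolled | Session | T1 | Infant age at T1 |
|---|---|---|---|---|
| Youngest case | 25 wk, 21 Dec | 1 Jan | 1 Mar | 25 + 70/7 − 40 = −5.0 wk (unborn) |
| Middle case | 29 wk, 8 Dec | 18 Jan | 18 Mar | 29 + 100/7 − 40 = 3.3 wk |
| Oldest case | 33 wk, 25 Nov | 4 Feb | 4 Apr | 33 + 130/7 − 40 = 11.6 wk |

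The middle woman's infant is 29 + 161/7 − 40 = 12.0 weeks old at T2 (18 May).

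**Step 3. Shares of the sample, by simulation.** Inputs from the article: the enrolment window, the entry range and the last session date. Assumptions for the base case: enrolment uniform over 25 Nov to 21 Dec; gestation uniform over 25w0d to 33w6d; birth at mean 39.3 weeks (SD 1.6); sessions uniform over 1 Jan to 4 Feb; T1 = session + 61 days; T2 = session + 122 days; the same clock in both arms.

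| Scenario | T1 unborn | T1 born, under 6 wk | T1 6 wk or older | Unborn or under 6 wk |
|---|---|---|---|---|
| Base case | 9.4% | 54.2% | 36.4% | 63.6% |
| All sessions 1 Jan, birth at 40 wk | 32.3% | 62.4% | 5.2% | 94.7% |
| All sessions 4 Feb, mean birth 38.5 wk (SD 2.0) | 0.7% | 29.3% | 70.0% | 30.0% |

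With sessions spread over 15 Jan to 4 Feb and the other base-case assumptions, 53% are unborn or under 6 weeks. A separate calculation with birth at 40 weeks, or at mean 39.5 (SD 1.5), and sessions over the whole window gave 65% to 71%. Its lowest value was 25%, with all sessions near 4 Feb and visits 10 days late.

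At T2 the base case has 98.7% at 6 weeks or older, and 93.9% in the early extreme.

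**Step 4. Illustrative dilution.** Assume true uptake by 6 weeks of 60% against 40%, a difference of 20 points, and count unborn and not-yet-vaccinated infants as no. In the base case at T1:

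- all doses given at birth: 20 × (1 − 0.094) = 18.1 points;
- doses spread evenly over 6 weeks: 13.2 points by simulation;
- half at birth, half spread: (18.1 + 13.2)/2 = about 15.7 points.

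T2 recovers about 20 points. An equal-weight average of T1 and T2 would be (18.1 + 20)/2 = 19.1 down to (13.2 + 20)/2 = 16.6 points. The uptake figures and dose timing are assumptions; only the direction follows from the schedule.

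**The case against.** A reader might infer that T1 BCG status is invalid, that no coding can rescue it, or that the primary outcome is lost. The documents do not support any of these.

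- A dose already given to a born infant is correctly recorded at T1, and receipt at birth can be known for every infant born by then. What is unsettled is the T1 negative and the 6-week classification.
- Vaccinated by T1, with all randomised women in the denominator, is a defined intention-to-treat quantity. With matching visit timing it is diluted, but it is not biased when there is no effect.
- Table 2 also measures BCG at T2, and a group-by-time model can give a T2 contrast. On the assumed 60% against 40%, power at T2 is about 97% with 185 per arm and about 90% with 130 per arm (30% attrition).
- Data Analysis speaks of the response variables without naming BCG, so an averaged BCG effect is permitted by the text but not fixed by it.
- The session start day and the gestational-age distribution are not given. Controls attend no session, and the Control Group section says the arms had different follow-up dates, so one clock for both arms is also assumed.

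All of this stands and sets the limits of the point. It could also be said that naming the decisive visit is a detail for a fuller document. That does not dispose of the point: the article itself gives an outcome defined by infant age a full T1 reading on a clock unrelated to birth.

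**Conclusion.** The point holds in limited form. T1 BCG status is incomplete for a substantial share of infants, probably most: about 64% in the base case and about 30% to 95% across the main scenarios. That most are under 6 weeks is the central result and not an established fact. That some are unborn runs from under 1% to 32%. Both depend on session dates, gestational-age spread and birth timing that the article does not state.

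The outcome itself survives, because nearly all infants are past 6 weeks at T2. The weakness is that the plan gives T1 and T2 equal standing for BCG and describes no BCG comparison beyond models over time. The cost of following it is a diluted effect and a time trend that is hard to interpret. Since results are not yet reported, this should be settled before the BCG comparison is run.

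**What to change.** 1. Name one primary BCG assessment. The simple choice is status at T2. Where birth and dose dates were recorded, the better choice is status at one fixed infant age, which the sponsor should reconcile with the two parts of the Table 2 definition (birth dose, delay after 6 weeks). The article does not say that these dates were collected, so T2 status is the fallback. Without dose dates, T2 status would also count doses given after 6 weeks, and the report should say so.
2. Compare the arms once, by a risk difference with 95% CI. If a fixed age is used and a few infants have not reached it at T2, a Kaplan-Meier proportion on the infant-age scale handles them.
3. In Table 2, mark the T1 BCG entry as descriptive or date collection only.
4. In Data Analysis, state that the repeated-measures and mixed models do not supply the primary BCG comparison. They can stay for the score outcomes.
5. Notify the registry and the ethics committee, as Ethical Considerations already promises for changes to outcomes or analysis methods.

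The cost is wording, plus use of birth and dose dates if they exist. No extra participants or visits are needed. The one small loss is that the 2-month BCG reading is no longer a primary efficacy estimate.
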